### Study Aims and Hypotheses

The primary outcomes of this RCT will be the impact of the iBFW, compared to a control writing condition, on diabetes distress and benefit-finding in diabetes. Our primary hypotheses are that adults with type 1 or type 2 diabetes randomized to receive iBFW will demonstrate significantly reduced diabetes distress and significantly increased benefit-finding for diabetes, compared to the control condition, at both one-month and three-month follow-ups.

Secondary outcomes will include symptoms of depression, symptoms of anxiety, diabetes self-care, health care utilization, and perceived self-health. Our secondary hypotheses are that compared to those in the control condition, the iBFW group will demonstrate significant: (1) reductions in depression symptoms; (2) reductions in anxiety symptoms; (3) increased diabetes self-care; (4) reduced number of visits to health professionals; and (5) improved perceived health, at both one-month and three-month follow-ups.

This study also aims to examine validation of the intervention instructions by investigating immediate emotional responses to the writing tasks, and the number of positive emotion words and cognitive insight words used in the writing tasks. It is hypothesized that compared to those in the control condition, the iBFW group will (1) show greater increases in positive affect postwriting, and (2) use more positive emotion words and more cognitive insight words than the control group.

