## Methods

### Study Design

A 2 (conditions) x 3 (time) RCT design is planned. A flow diagram for the trial is shown in Figure 1. Participants will be randomized to either iBFW or an Internet-based control writing condition. Both conditions involve an intervention of 3 days of online writing. Outcomes will be assessed at 3 time points for both groups: baseline, one-month, and three-months postintervention. We will also assess self-rated current mood immediately prior to and following each writing session, and administer three survey questions (assessing how personal, meaningful, and distressing the writing exercise was) after each writing task. An online *Feedback Questionnaire* to assess user satisfaction and perceived helpfulness will also be administered postintervention.

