Outcome data at the one-month and three-month follow-up time-points will be analyzed on an intention-to-treat basis using linear mixed modelling, with time-points as a within-group factor and intervention as a between-group factor. The interaction of time and study condition will be examined in each analysis, as a significant interaction will indicate a group difference in the pattern of change over time in the outcome of interest. Significant interactions will be explored using Bonferroni adjusted comparisons of the two groups at one-month and three-month follow-ups. All effects will be tested at *P*<.05. Within-group and between-group Cohen *d* effect sizes will be calculated.

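### The hypothesised group differences at one and three months are tested only after a significant time-by-condition interaction, and with no baseline term named, which loses power that baseline-adjusted contrasts would recover

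*Protocol article*

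**What the plan says.** Under Study Aims and Hypotheses, the primary hypotheses are lower diabetes distress and higher benefit-finding with the writing intervention, "compared to the control condition, at both one-month and three-month follow-ups". The target is therefore a between-group difference at each of two named times.

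Under Study Design, "A 2 (conditions) x 3 (time) RCT design is planned", and the three times are baseline, one month and three months. Table 1 shows both primary scales collected at all three.

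Under Statistical Analyses, outcomes are analysed "using linear mixed modelling, with time-points as a within-group factor and intervention as a between-group factor". No other model term is named. The test that comes first is fixed: "The interaction of time and study condition will be examined in each analysis". The group comparisons depend on it: "Significant interactions will be explored using Bonferroni adjusted comparisons of the two groups at one-month and three-month follow-ups". The level is also fixed: "All effects will be tested at *P*<.05". Within-group and between-group Cohen d values are promised without any condition.

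**The concern.** The hypothesis asks two direct questions: do the arms differ at one month, and do they differ at three months? The plan answers them only after a 2-df test of whether the arms differ in their pattern over three times. A true difference at both follow-ups can fail at that gate, and its comparisons are then never tested.

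If the gate is passed, the comparisons at each follow-up come from a model whose only stated terms are time and condition. In such a model, with complete data, the group comparison at one time is the plain difference between arm means at that time. It carries any chance baseline difference and all the between-person variance that the baseline score could explain. Both baseline scores are already collected, so the loss is avoidable. It matters more because the trial is small and expects up to half its participants to drop out.

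**Working it through.** **Inputs from the article.** From Sample Size: d=.7, power .80, P<.05, one-tailed, 26 evaluable per group, attrition up to 50%, target 104. From Statistical Analyses: interaction at .05, then two comparisons under Bonferroni, so .05/2 = .025 each.

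**Inputs assumed.** d=.7 at both follow-ups, 26 completers per arm, unit variance at each time, and one correlation ρ between every pair of times. The article gives no correlation, so I use .4, .5, .6 and .7. All tests below are two-sided unless stated.

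**1. The plan's own figure.** n per group = 2(1.645 + 0.842)²/0.7² = 12.37/0.49 = 25.2, so 26. Exact noncentral-t power at 26 per group, one-sided .05, is .801. With 50% attrition, 26/0.5 = 52 per group and 104 in total. The figure reproduces, but for one simple two-group comparison, which is not the planned analysis.

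**2. The gate.** With baseline as a level of time, the 2-df interaction has power of about .65/.73/.83/.92 for ρ = .4/.5/.6/.7 (noncentral F, compound symmetry). It is below .80 at ρ = .5 and above it at ρ = .6.

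**3. The unadjusted comparison at one follow-up.** Noncentrality = 0.7 × √(26/2) = 2.52. At .025 the power is .587, whatever ρ is.

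**4. The baseline-adjusted comparison at one follow-up.** Adjustment multiplies the residual variance by 1 − ρ², so the noncentrality becomes 2.52/√(1 − ρ²) = 2.75/2.91/3.15/3.53. At ρ = .6 the unadjusted estimate has 1/(1 − .36) = 1.56 times the variance of the adjusted one.

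**5. Whole procedures, simulated** (20,000 or more trials per correlation; runs agree to about .01), every follow-up comparison at .025:

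| | ρ=.4 | .5 | .6 | .7 |
|---|---|---|---|---|
| Three months: planned (gate, then unadjusted) | .42 | .46 | .51 | .55 |
| Three months: unadjusted, no gate | .59 | .59 | .59 | .59 |
| Three months: baseline-adjusted, no gate | .66 | .72 | .79 | .88 |
| Both follow-ups: planned | .29 | .34 | .38 | .43 |
| Both follow-ups: baseline-adjusted, no gate | .48 | .56 | .65 | .79 |

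**6. Reading the table.** For a single three-month comparison, adjustment alone adds .07/.13/.20/.29 over the unadjusted, ungated test. The gate alone takes away .17/.13/.08/.04. For both follow-ups, as hypothesised, the combined gain is .19/.22/.27/.36. Because every row uses .025, none of this comes from relaxing the multiplicity rule.

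**The case against.** The strongest reply is that this is a conventional analysis. It does not inflate type I error, the trial calls itself partly exploratory, and the article condenses a fuller plan that may specify covariates. The interaction uses baseline, because with three times it works on change from baseline. The group comparisons at one and three months are written into the plan. The Cohen d values are promised whatever the interaction shows, so effects will be reported even if the gate fails. Participants with only one follow-up would also add information beyond 26 completers per arm.

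Most of this stands and limits the point to efficiency and fit with the hypothesis. It does not remove it. The article itself fixes the first test, the precondition and the comparisons that follow. If a fuller plan adds a baseline covariate, the gate still remains. The pilot label does not help either, because Sample Size claims .80 power for d=.7, and the planned route does not reach that for the stated hypothesis under these assumptions.

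Three stronger readings are tempting and are not supported:

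- **Time has two levels.** The sentence beginning "Outcome data at the one-month and three-month follow-up time-points will be analyzed on an intention-to-treat basis" could be taken to mean that only the follow-ups enter the model. The interaction would then ask only whether the effect changes between one and three months, and with a constant effect its power would be 5%. The 2 x 3 design, and the plan's own description of the interaction as a group difference in change over time, point to three levels. The wording is loose, but 5% is not the trial's power.
- **Baseline imbalance produces false positives.** Chance imbalance can contribute to a significant interaction, but under randomisation this is already within the nominal 5%.
- **The gain is larger still.** Setting adjusted contrasts at .05 against planned ones at .025 (for example .68 against .33 for both follow-ups at ρ = .5) credits baseline adjustment with what comes from dropping Bonferroni. The equal-level figures above are the fair comparison.

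**Conclusion.** The point holds as one of efficiency and fit, and should be acted on. The planned procedure is valid, but it reaches the hypothesised differences through an unnecessary gate and then tests them without using the baseline scores. At a common .025 level, power to show a difference at both follow-ups is about .29 to .43 as planned and .48 to .79 with adjusted, ungated contrasts, for correlations from .4 to .7. At three months alone the figures are .42 to .55 and .66 to .88.

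The sizes depend on d=.7 at both follow-ups, 26 completers per arm and equal correlations. The correlation is not in the article, so the exact gain is unknown. The adjusted route is ahead throughout the range examined, and its lead grows with the correlation.

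**What to change.** In Statistical Analyses:

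1. Make the primary analysis a linear mixed model of the one- and three-month scores with baseline score, time, condition and time x condition as fixed terms. A model of all three times with arm means constrained equal at baseline serves the same purpose.
2. Name the adjusted group difference, with 95% CI, at each follow-up as the primary contrast for each primary outcome.
3. Remove the requirement of a significant interaction and report the interaction descriptively.
4. Reword the opening sentence on outcome data so that it states where baseline enters and cannot be read as an interaction over the two follow-ups only.

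Whether to keep Bonferroni, or to test each follow-up at .05 and require both, is a separate decision that should be stated. Diabetes type as a further covariate is optional.

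The cost is a change of analysis wording, with no new data or participants. The article reports the trial as still collecting data, so the change could be made and dated before analysis.

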### Trial Status

The trial is currently in the data collection phase. Recruitment to the study commenced in February 2015. Results are expected by July 2017.

## Discussion

This study will be the first to examine benefit-finding writing for adults with type 1 or type 2 diabetes. The feasibility and efficacy of this brief intervention will be evaluated in a two-arm RCT, with a three-month follow-up period, in which iBFW for diabetes is compared to an active control condition (use-of-time writing). The participants in this study will be adults with type 1 or type 2 diabetes who may be experiencing diabetes distress and/or mild symptoms of depression or anxiety. Participants with both type 1 and type 2 diabetes will be included in this study, as perceived benefits of living with diabetes have previously been reported by both people with type 1 diabetes [55] and type 2 diabetes [83]. Outcomes assessed will include multiple psychological and diabetes-specific variables, including the primary outcomes of diabetes distress and benefit-finding for diabetes, and secondary outcomes of symptoms of depression and anxiety, diabetes self-care, perceived health, and health care utilization. Furthermore, we will investigate validation of the intervention by examining immediate emotional responses to the writing tasks and conduct linguistic analyses of the writing scripts.

Results from this trial will contribute to the growing body of knowledge about a more recent form of therapeutic writing, known as benefit-finding writing. The limited research on benefit-finding writing to date suggests that it may have the same health benefits of the more commonly researched EW, but with the advantage of increased positive affect immediately following the intervention.

Limitations to this study include the brevity of the follow-up period (three months) and the reliance on self-reported data. Physiological data, such as HbA1c or other indicators of blood glucose level, are not included in this study. The included outcome of health utilization has limitations itself, as participants may not visit health professionals frequently enough for any changes to be detected in the follow-up period of three months. Furthermore, it is unclear as to whether decreased health care utilization is a positive outcome, given that going to an appropriate health professional when a need exists is a good thing [84]. Nevertheless, we have included assessment of this outcome as any changes in health care utilization in people with diabetes would be of interest, and previous trials of EW and benefit-finding writing have reported reductions in health care utilization [42,84].

Similar to many RCTs, the generalizability of our results is restricted by the exclusion criteria. For example, adults with diabetes currently experiencing depression of moderate or greater severity will be excluded from this trial; hence the results will not be able to be generalized to people with diabetes who are currently depressed. Furthermore, the sample size (N=104) will enable the detection of a moderately large effect size, in line with some previous studies of benefit-finding writing [42], but will not allow for the detection of small effect sizes reported in meta-analyses of writing interventions. However, as recommended in a recent comprehensive review of therapeutic writing [31], when investigating new writing interventions in new clinical populations, it is prudent to first conduct feasibility studies and pilot trials. Thus, this novel study will enable a preliminary investigation of the feasibility and efficacy of benefit-finding writing for adults with diabetes.

If the iBFW is found to be helpful for people with type 1 or type 2 diabetes, this intervention will offer the potential to be a low-cost, easily accessible public health intervention to improve the well-being of large numbers of diabetic patients with lower-level psychological needs. Furthermore, benefit-finding writing may also have the potential to assist other populations with chronic conditions.

## Appendix

Multimedia Appendix 1 Instructions for Internet-based benefit-finding writing (iBFW) for diabetes.

## Abbreviations

DDS17: Diabetes Distress Scale
EW: expressive writing
GAD-7: Generalized Anxiety Disorder-7
HbA1c: hemoglobin A1c
iBFW: Internet-based benefit-finding writing
I-PANAS-SF: International Positive and Negative Affect Schedule Short Form
PANAS: Positive and Negative Affect Schedule
PHQ-9: Patient Health Questionnaire-9
RCT: randomized controlled trial
